# Improving Diabetes Equity and Advancing Care (IDEA) to optimize team-based care at a safety-net health system for Black and Latine patients living with diabetes: study protocol for a sequential, multiple assignment, randomized trial

**DOI:** 10.1186/s13063-024-08346-9

**Published:** 2024-07-24

**Keywords:** Diabetes, Diabetes self-management training, Community health worker, Remote glucose monitoring, Chronic disease, Sequential multiple assignment randomized trials (SMART), Health equity

## Abstract

**Background:**

Diabetes is the eighth leading cause of death in the USA. Inequities driven by structural racism and systemic oppression have led to racial/ethnic disparities in diabetes prevalence, diagnosis, and treatment. Diabetes-self management training (DSMT), remote glucose monitoring (RGM), and tailored support from a community health worker (CHW) have the potential to improve outcomes. This study will examine the implementation of these interventions in a safety-net healthcare setting.

**Methods:**

Using implementation science and racial equity principles, this study aims to (1) evaluate the appropriateness; (2) measure fidelity; and (3) compare the effectiveness of varying the combination and sequence of three interventions. An exploratory aim will measure sustainability of intervention adherence and uptake. This mixed-methods trial employs a sequential, multiple assignment randomized trial (SMART) design, patient focus group discussions, and staff interviews. Eligible Black/Latine patients will be recruited using patient lists extracted from the electronic medical record system. After a detailed screening process, eligible patients will be invited to attend an in-person enrollment appointment. Informed consent will be obtained and patients will be randomized to either DSMT or RGM. At 6 months, patients will complete two assessments (diabetes empowerment and diabetes-related distress), and HbA1c values will be reviewed. “Responders” will be considered those who have an HbA1c that has improved by at least one percentage point. “Responders” remain in their first assigned study arm. “Nonresponders” will be randomized to either switch study arms or be paired with a CHW. At 6 months participants will complete two assessments again, and their HbA1c will be reviewed. Twelve patient focus groups, two for each intervention paths, will be conducted along with staff interviews.

**Discussion:**

This study is the first, to our knowledge, that seeks to fill critical gaps in our knowledge of optimal sequence and combinations of interventions to support diabetes management among Black and Latine patients receiving care at a safety-net hospital. By achieving the study aims, we will build the evidence for optimizing equitable diabetes management and ultimately reducing racial and ethnic healthcare disparities for patients living in disinvested urban settings.

**Trial registration:**

ClinicalTrials.gov: NCT06040463. Registered on September 7, 2023.

**Supplementary Information:**

The online version contains supplementary material available at 10.1186/s13063-024-08346-9.

## Introduction

### Background and rationale {6a}

Diabetes is the eighth leading cause of death in the USA and can lead to heart disease, vision loss, kidney disease, and ultimately death [1]. The American Diabetes Association estimates the cost of diabetes due to treatment and lost productivity to be $327 billion in 2017, a 26% increase since 2012 [2]. Racial and ethnic diabetes prevalence, diagnosis, and treatment disparities are widespread and well-documented [3]. Health and social inequities, driven by structural racism and systemic oppression, lead to a lack of safe and secure housing, nutritious and accessible food, reliable transportation, and healthcare access, which can predict poor disease outcomes. In Chicago, 11.3% of adults are living with diabetes, with Black and Hispanic Chicagoans disproportionately affected [4]. In 2022, Hispanic individuals were nearly three times more likely and Black individuals more than twice as likely to have diabetes compared to their White counterparts (14.7%, 12.5% and 5.5%, respectively) [4]. Substantial disparities also exist in diabetes-related hospitalization; Hispanic individuals had double the rate and Black individuals almost four times the rate of diabetes-related hospitalizations compared to White individuals (25.3 per 10,000, 40.3 per 10,000 and 12.5 per 10,000, respectively) [5].

There are several evidence-based diabetes management practices such as dietary changes, increased physical activity, and lifestyle education programs. Team-based care (TBC) is one systems-level care model that has been shown to be effective in managing hemoglobin A1c (HbA1c), blood pressure, and cholesterol among patients with diabetes [6–8]. The Institute of Medicine defines TBC as one in which a patient’s care team include the patient, the patient’s primary care team, and at least one other health care provider [9]. While randomized controlled trials and meta-analyses have demonstrated the effectiveness of TBC, less is known about the impact of particular TBC enhancements, the sequencing of those enhancements on outcomes, and their effectiveness among uninsured patients residing in historically disinvested communities [7]. Given the complex interplay of health and social determinants, there is no one-size-fits-all approach when it comes to addressing chronic diseases such as diabetes. Solutions must address all interrelated factors and consider the uniqueness of each patient.

Three interventions that support and/or teach diabetes management strategies and can ultimately reduce HbA1c are diabetes-self management training (DSMT), remote glucose monitoring (RGM), and tailored support from a community health worker (CHW). DSMT teaches individuals how to live with and manage a diabetes diagnosis and has been proven to increase participant lifestyle change, reduce blood glucose levels, HbA1c, and lipid profiles [10]. RGM is an automated process of transmitting blood glucose information directly to a health care provider using a mobile application. RGM relies on valid and reliable blood glucose measures which are measured by the patient outside of a healthcare setting. Measures come from a glucometer or insulin pump, which are regulated by the United States Food and Drug Administration (FDA). The FDA requires 95% of readings from all self-monitoring glucose devices to be accurate within 15–20% above or below the true reading [11, 12]. The literature on RGM is not extensive, but has shown promise for improving glycemic control [13–15]. Finally, CHWs are specially trained, trusted members of the community that have been integrated into healthcare settings to provide tailored support to patients related to social needs and reinforcing education and lifestyle changes [16].

#### Framework

This study is guided by implementation science and racial equity principles. Implementation science seeks to explore the systematic uptake or improvement of an evidence-based practice into real-world practice. Employing implementation science principles facilitates a deeper understanding of the challenges around successfully delivering innovations in real-world settings. In recent years, implementation science has become a frequently used way of thinking to improve policies and practices within health care settings. Similarly, the public health community, healthcare institutions, and policymakers have become more familiar with racial and health equity principles and their potential to reduce health and healthcare-related disparities among racial and ethnic minorities. Implementation science experts have called for health services research to prioritize health equity.

This study integrates Proctor et al.’s Outcomes for Implementation Research framework and Kilbourne’s Advancing Health Disparities Research framework to present a conceptual model (Fig. 1. IDEA Study Conceptual Framework) for rigorous measurement of implementation, service, and patient outcomes with an equity lens [17, 18]. Kilbourne proposes three phases of advancing health disparities research: (1) *detecting* the health disparities and identifying the disinvested populations; (2) *understanding* the determinants of these health disparities at varying levels of our healthcare system; and (3) *reducing* disparities by intervening, evaluating, translating, and disseminating findings. The present study focuses on *reducing* disparities. The implementation outcomes of interest are *appropriateness* of each of the three interventions, *fidelity* to intervention adherence, and *sustainability* of disease management strategies. Appropriateness refers to the perceived fit or compatibility of these strategies for the patient population, their needs, and for the setting. Fidelity refers to the degree to which the strategy is implemented as intended. Sustainability refers to the extent to which the treatment is sustained or institutionalized.

**Fig. 1 Fig1:**
[figure not shown]
IDEA Study Conceptual Framework

### Objectives {7}

This study seeks to achieve the following aims:

Aim 1: Evaluate the appropriateness of DSMT, RGM, and high-touch, individualized CHW support from the provider and patient perspectives.Aim 2: Measure fidelity of DSMT, RGM, and high-touch, individualized CHW support for Black/Latine patients with diabetes in a safety-net hospital setting.Aim 3: Compare the effectiveness of varying the sequence of three enhancements (DSMT, RGM, and high touch, individualized CHW support) to reduce HbA1c among Black/Latine patients with diabetes.Exploratory Aim 3a: Measure the extent to which high-touch, individualized CHW support reinforces DSMT concepts and RGM uptake and adherence for Black/Latine patients with diabetes (sustainability).

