#### Community health worker support

CHWs will be introduced 6 months into the trial at rerandomization for participants whose HbA1c has not improved by at least one percentage point (Fig. 2. IDEA Study SMART Design). All patients paired with a CHW will be screened for social needs utilizing a standard social determinants of health (SDoH) screening tool, will receive referrals to resources to address unmet social/health needs, and will be actively navigated to health and social service resources as appropriate.

For participants originally randomized to the RGM intervention, the CHWs will focus on enhancing uptake and use of the Glooko application. During the initial in-person visit with the CHW, which will take place either at the clinic or in the participant’s home, the CHW will screen for SDoH needs, provide referrals to address unmet needs, and assess participant barriers to regularly measuring and/or reporting glucose levels using Glooko (e.g., connection issues between device and phone, barriers to transmitting information to provider). The CHW will also support the patient in overcoming barriers through individualized education, motivational interviewing, goal-setting, and trouble-shooting technological and resource challenges. Following the initial visit, the CHW will follow up with the patient at least monthly by phone for 6 months to assess adherence with RGM, trouble shoot additional barriers, and reinforce education concerning the Glooko application. The CHW will also provide active support to the participant in connecting with resources to support health and social needs. Additional in-person visits will occur during the time interval as needed.

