Randomization envelopes were created for the second round of randomization at 6 months following a similar protocol. In this case, the staff member printed 60 pieces of paper that say “CHW,” 60 pieces of paper that say “RGM,” 60 pieces of paper that said DSMT, and 60 pieces of paper that say “CHW + RGM.” We assumed that a certain number of participants would improve by at least one percentage point and would not be randomized. After creating the 240 envelopes, the staff member created two boxes of envelopes, stratified by the initial treatment assignment. In the first box, for participants initially assigned to DSMT, the staff member shuffled and placed the CHW and RGM envelopes in the box marked “DSMT.” In the second box, for participants initially assigned to RGM, the staff member shuffled and placed the remaining DSMT and CHW + RGM envelopes in the box marked “RGM.”

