#### Secondary outcomes

For secondary outcomes, including implementation outcomes (fidelity, appropriateness, sustainability) and patient-centeredness, we will use a combination of qualitative and quantitative methods. Descriptive statistics will summarize categorical variables as frequencies and percentages and continuous variables as means with standard deviations or medians with interquartile ranges. Fidelity to the interventions will be assessed by measuring RGM adherence (data uploads and blood glucose entries in Glooko), DSMT attendance rates, and CHW engagement (completion rates of initial education sessions, SDoH screeners, and follow-up meetings). Logistic regression will identify predictors of adherence.

Appropriateness and sustainability will be evaluated through qualitative analysis of focus group and interview data, which will be transcribed, coded, and analyzed thematically. Quantitative analyses will compare scores from validated surveys (Short Form-Diabetes Empowerment Scale (SF-DES) and Problem Areas in Diabetes (PAID)) between groups using paired *t*-tests or Wilcoxon signed-rank tests for within-group comparisons and independent *t*-tests or Mann–Whitney *U* tests for between-group comparisons.

In our secondary analysis, patients in treatment scenarios D or F will complete the DES-SF and PAID at 6 and 12 months, with scores compared between treatment scenario groups using a paired *t*-test or paired Wilcoxon test. For exploratory analysis, we will follow the same process, though our focus will be on assessing trends in both primary and secondary outcomes due to potential limitations in statistical power from the addition of the CHW enhancement.

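### Exploratory Aim 3a asks how far CHW support reinforces DSMT and RGM use, but the only randomised contrast involving the CHW is CHW versus switching, which does not isolate a CHW effect

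*Protocol article*

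**What the plan says.** The Objectives section sets Exploratory Aim 3a, tagged as sustainability: "Measure the extent to which high-touch, individualized CHW support reinforces DSMT concepts and RGM uptake and adherence". The Community health worker support section describes the matching activity. For the RGM-first arm "the CHWs will focus on enhancing uptake and use of the Glooko application", and for the DSMT-first arm the CHW goes back over the main DSMT messages.

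The second-stage options are fixed in three places:

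- The abstract's Methods say that non-responders "will be randomized to either switch study arms or be paired with a CHW", while responders "remain in their first assigned study arm".
- Community health worker support limits who can receive a CHW: "CHWs will be introduced 6 months into the trial at rerandomization for participants whose HbA1c has not improved by at least one percentage point".
- Sequence generation {16a} gives the envelopes. For the DSMT-first box, "the staff member shuffled and placed the CHW and RGM envelopes in the box marked"; for the RGM-first box, "the staff member shuffled and placed the remaining DSMT and CHW + RGM envelopes in the box marked". There are 60 envelopes of each of the four kinds.

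The Secondary outcomes part of the statistical methods compares the DES-SF and PAID scores of patients in scenarios D or F with a paired test. It says the exploratory analysis will look at trends "due to potential limitations in statistical power from the addition of the CHW enhancement". The Limitations section does not mention the missing comparator.

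**The concern.** To say how far a CHW reinforces an earlier intervention, one needs to know what would have happened to similar patients who had that intervention and no CHW. In this trial every CHW recipient is a non-responder, and everyone who stays on the first intervention without a CHW is a responder. CHW support and 6-month response are therefore completely separated, apart from the patients who were switched.

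At stake is the interpretation of Aim 3a. A report could say that CHW support did, or did not, sustain DSMT learning or RGM use on the strength of a comparison that cannot show it. Power is the only limit the plan names, so a reader may conclude that a larger trial of the same design would answer the question.

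**Working it through.** **1. The plan's own figure.** No sample size is given for Aim 3a. The stated one belongs to the six-group ANOVA on HbA1c change. With k = 6, f = 0.25 and alpha = 0.05, the noncentrality at N = 216 is f² × N = 0.0625 × 216 = 13.5, and power is 0.811 (N = 210 gives 0.798). With 20% dropout, 216 / 0.8 = 270. Both figures reproduce, and nothing below alters them.

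**2. The second-stage options.**

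| First arm | Responders | Non-responders, option 1 | Non-responders, option 2 |
|---|---|---|---|
| DSMT | stay in DSMT | CHW | switch to RGM |
| RGM | stay in RGM | CHW + RGM | switch to DSMT |

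None of the four non-responder options is to continue the first intervention alone. The text settles this without the design figure.

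**3. What the randomised contrast estimates.** Among non-responders in one first arm, let m be the mean 12-month score had they continued alone, m + C the mean with a CHW, and m + S the mean after switching. The contrast is (m + C) - (m + S) = C - S. Assume C = 0.25 SD for illustration:

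- S = 0: 0.25 - 0 = +0.25 SD
- S = 0.25: 0.25 - 0.25 = 0
- S = 0.50: 0.25 - 0.50 = -0.25 SD

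The contrast is valid for CHW against switching, but its sign does not give the sign of C. Sample size does not enter the expression.

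**4. RGM use.** The randomised partner of CHW + RGM has been switched to DSMT, so its RGM use says nothing about what RGM use would have been without the CHW.

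**5. The non-randomised contrasts.** Comparing CHW recipients with responders compares groups defined by a post-baseline outcome, with no overlap in 6-month response. Change from 6 to 12 months within a CHW path has no concurrent control, so it absorbs time trends and any regression to the mean that follows selection on the 6-month result.

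**6. Is the power caveat true?** Take 216 evaluable patients, 108 per first arm, split equally between the two options. The non-response rate is not given, so assume 50% to 90%.

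- 50%: 108 × 0.5 / 2 = 27 per option; detectable difference at 80% power 0.78 SD; power for 0.5 SD 44%.
- 90%: 108 × 0.9 / 2 = 48.6 per option; detectable difference 0.57 SD; power for 0.5 SD 68%.

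Power is limited even for CHW versus switching, so the caveat is correct as far as it goes.

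**The case against.** The strongest reply is that the plan promises no isolated CHW effect. Aim 3a is exploratory, speaks of measuring an extent, carries no hypothesis, and is analysed for trends. Sustainability is also to be studied qualitatively, and eight of the twelve focus groups follow rerandomisation. This stands and limits the weight of the point. It does not remove it: to reinforce is causal language, and nothing in the plan tells the reader that the trial's comparisons cannot support it. Focus groups can describe how CHW support helped, but they do not give a controlled estimate.

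Second, DSMT is four sessions, one every other week, so it would normally be over well before month 6. Continuing DSMT alone would then largely mean no further intervention, and DSMT then RGM is an informative randomised comparator in which nobody goes back over DSMT content. This also stands, but RGM may itself move SF-DES or PAID, so the contrast remains C - S.

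Some stronger readings are tempting but unsupported:

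- A reader might infer that the design is faulty or that Aim 3 fails. Augment-or-switch is a coherent SMART question, and the regime comparison does not need a continue-alone group.
- A reader might infer that the power caveat is wrong. It is true but incomplete, and the plan does not say that power is the only limit.
- A reader might try to size the bias by setting CHW + RGM non-responders against RGM responders. The protocol plans no such comparison, and any figure would rest entirely on assumed response and usage rates, so none is given here.

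**Conclusion.** The point holds in a limited form. The documents' text alone establishes that no randomised group continues the first intervention without a CHW. It follows that the randomised evidence bearing on Aim 3a is CHW versus switching for SF-DES and PAID, and that RGM use has no randomised comparator. This structural conclusion needs no numerical assumption. The C - S values and the 50% to 90% non-response range are illustrations, not document figures.

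The consequence is confined to the wording and analysis of one exploratory aim. Aim 3, the SMART design and the 216/270 sample size are unaffected.

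The planned analysis does not supply the missing comparison. A paired test cannot compare different patients. Trial design {8} labels DSMT to CHW as path E, and only two of the six paths contain a CHW, so scenarios D and F cannot both be CHW paths. That labelling is a separate matter and needs its own reconciliation.

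**What to change.** 1. For Aim 3a, compare SF-DES and PAID between the randomised second-stage options within each first arm: DSMT then CHW against DSMT then RGM, and RGM then CHW + RGM against RGM then DSMT. Use a between-group analysis; the independent-sample tests already listed under Secondary outcomes are of the right kind. Word the conclusion as CHW compared with switching.
2. Report RGM use in the CHW + RGM path, months 1-6 beside months 7-12, as descriptive only, and do not attribute any change to the CHW.
3. In Secondary outcomes keep the power caveat and add that no randomised group continues the first intervention without a CHW, so a larger sample would not isolate the CHW effect.

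The cost is wording and one exploratory analysis. No patients or visits are added. The outcomes table already schedules both scales at 6 and 12 months, and the monthly Glooko reports already cover RGM use. The downside is a more modest aim.

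A continue-alone option is not proposed. It would change the design: with eight groups, the plan's own ANOVA method needs 240 evaluable patients (power 0.807), or 240 / 0.8 = 300 recruited.

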### Trial design {8}

This study uses a sequential, multiple assignment, randomized trial (SMART) design with approximately 270 Black/Latine patients living with diabetes recruited from two locations of a diabetes and endocrinology clinic (“the Center”) in Chicago, IL. A SMART is a type of adaptive trial that uses at least two points of randomization to build the evidence for an optimal intervention or treatment. In the IDEA study SMART, we will test three components of a team-based care model that provides diabetes care and management for patients living with diabetes and other complex health and social needs. HbA1c will serve as our pre-planned tailoring variable which will determine participant rerandomization. At 6 months, participants with an HbA1c of at least one percentage point improvement from their baseline measurement will be considered “responders”; participants with an HbA1c that has not improved by at least one percentage point from their baseline measurement will be considered “non-responders”. The study will be conducted by Sinai Urban Health Institute (SUHI), the community-engaged research institute within Sinai Chicago, a safety-net health system in Chicago, IL. See Fig. 2. IDEA Study SMART Design, for the study design. We hypothesize that path E (DSMT to CHW) will have the largest reduction in A1c compared to all other paths. DSMT provides actionable education and guidance for improving diabetes management, whereas RGM focuses on information tracking for both patients and providers. The CHW will reinforce information taught during DSMT sessions.

